### Outcome measures and subjects’ timelines

#### Outcome measures

##### Baseline information

Demographic information will be collected using a custom-made, standardized survey form that includes age, gender, educational background, occupation, weight, and height.

Surgical procedure information will be collected using a custom-made, form that collects information regarding clinical characteristics, including surgery and anesthesia duration, blood loss during surgery, infusion volume during surgery, and vital signs during surgery (body temperature, cardiac rate, breathing rate, and blood pressure).

##### Primary outcome

The time until the first postoperative flatus will be calculated, beginning at the time the subject returns to the ward after surgery. The subjects and their family members will be told to keep a record of the time until the first postoperative flatus:

Time until the first postoperative flatus = the moment of the first postoperative flatus – the moment when the subject returned to the ward after surgery

##### Secondary outcomes

*First postoperative defecation:* The time until the first postoperative defecation will be recorded, beginning at the time when the subject returns to the ward after surgery. The subjects and their family members will be instructed to record the time of the first postoperative defecation:

Time of the first postoperative defecation = the moment of the first postoperative defecation – the moment when the subject returned to the ward after surgery

*Abdominal pain:* A VAS will be used to estimate the level of the subjects’ postoperative abdominal pain [21]. The first assessment will be performed 6 h after the laparoscopic surgery, ahead of the first treatment. Thereafter, pain will be assessed every 12 h until a total of seven evaluations have been performed. The subjects and their families will assist in keeping the abdominal pain record.

*Abdominal distension:* A Likert scale will be used to evaluate the subjects’ abdominal distention after surgery [22]. The first assessment will be performed 6 h after laparoscopic surgery, ahead of the first treatment. Thereafter, distention will be assessed every 12 h until a total of seven evaluations have been performed. The subjects and their families will assist in keeping the abdominal distension record.

*Nausea:* A VAS scale will be used to evaluate the level of the subjects’ nausea [21]. The first assessment will be performed 6 h after laparoscopic surgery, ahead of the first treatment. Thereafter, nausea will be assessed every 12 h until a total of seven evaluations have been performed. The subjects and their families will assist in keeping the nausea record.

*Vomiting:* We will evaluate the number of times the subject vomits after surgery. The first assessment will be conducted 6 h after laparoscopic surgery, ahead of the first treatment. Thereafter, assessments will be performed every 12 h until a total of seven evaluations have been performed. The subjects and their families will assist in keeping the vomiting record.

*Ghrelin test:* Blood will be drawn for ghrelin testing once before surgery and again before discharge from the hospital. A total of 3 mL of blood will be collected from a vein in the morning, when the subject has an empty stomach. The blood sample will be allowed to sit for 30 min at room temperature and then be centrifuged at 3500 rpm for 10 min. The supernatant will be cryopreserved for ghrelin testing.

*Psychological status:* We will use the Hospital Anxiety and Depression Scale (HADS) to evaluate the subjects’ psychological status [23]. HADS has 14 items, of which seven evaluate depression and seven evaluate anxiety. To determine the severity of each condition, the depression and anxiety subscale scores are divided into categories of 0–7 points (asymptomatic), 8–10 points (symptoms suspected), and 11–21 points (symptoms indicated). The first assessment will be performed 6 h after laparoscopic surgery. Another HADS assessment will be performed on the day of discharge from the hospital.

*Quality of life:* We will use the Gastrointestinal Quality of Life Index (GIQLI) to evaluate the subjects’ quality of life [24]. The GIQLI was specifically designed to evaluate quality of life in subjects with gastrointestinal syndromes. It includes five aspects: subjective symptoms, physiological functions, daily life, social activities, and psychological/emotional state. There are 36 items in total, each adding 0–4 points to the score. Thus, the highest possible score is 144 points; higher scores indicate better quality of life. A normal score is in the range 121–125. The GIQLI will be evaluated three times. The first assessment will occur 6 h after the laparoscopic surgery; the second will occur on the day of discharge from the hospital, and the third will occur 1 month after discharge from the hospital.

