### Intervention

After laparoscopic surgery, the subjects will be asked to lie in the supine position without a pillow, and without eating or drinking. They will begin a liquid diet on the second day after surgery. The two groups will receive XNKQAT intradermal needling or sham stimulation 6 h after the surgery. Treatment will be repeated every 12 h thereafter until a total of six treatments have been administered. Each treatment will last for 3 min. Each time, the intradermal needles (or sham needles) will be attached to the surface of the acupoints. Six hours after surgery, immediately before the first treatment, the first evaluation will be carried out. The subjects will be evaluated every 12 h thereafter until a total of seven evaluations have taken place. Acupoints will be located in accordance with the World Health Organization Standard Acupuncture Point Locations in the Western Pacific Region [20]. The acupoints used will be PC6, DU26, and SP6. The nurse administering the treatment will stand next to the subject’s bed and help them to find a comfortable supine position.

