##### Subjects’ timeline

One day before a given subject’s laparoscopic surgery, the investigators will decide whether to include them in the trial. This will be considered day 0 of the experiment. The subjects will receive their first postoperative intervention 6 h after surgery. Thereafter, interventions will be repeated every 12 h until a total of six interventions have taken place. The first evaluation will occur on day 0. Evaluations will then take place after each intervention, for a total of seven evaluations. For an overview of the recruitment timeline, interventions, and subject assessment, see Fig. 2.

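### GIQLI and HADS are first scored 6 h after surgery, and for the GIQLI that score is a level of the repeated-measures ANOVA; adding a pre-operative score as covariate is a cheap, minor improvement

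*Protocol article*

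**What the plan says.** Secondary outcomes, Quality of life: "The GIQLI will be evaluated three times". Of the first it says "The first assessment will occur 6 h after the laparoscopic surgery"; the others are on the day of discharge and 1 month after it. The same paragraph lists daily life and social activities among the five areas the index covers.

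Secondary outcomes, Psychological status (HADS): "The first assessment will be performed 6 h after laparoscopic surgery. Another HADS assessment will be performed on the day of discharge from the hospital". Neither paragraph mentions a pre-operative score.

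Condition at that time: surgery is under general anaesthesia (Inclusion criteria), and afterwards subjects are "asked to lie in the supine position without a pillow, and without eating or drinking" (Intervention).

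Pre-operative contact: on the day before surgery "the investigators will decide whether to include them in the trial" (Subjects' timeline). One other secondary outcome already has a pre-operative value: "Blood will be drawn for ghrelin testing once before surgery and again before discharge from the hospital" (Ghrelin test).

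Analysis procedures: the GIQLI is analysed by repeated-measures ANOVA. HADS scores and categories are recorded, and the categories are tested by Mann–Whitney U or Spearman's rank correlation.

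The Subjects' timeline defines the day before surgery as day 0 and places the first evaluation on day 0. Design, Intervention and Secondary outcomes place it 6 h after surgery.

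**The concern.** Six hours after general anaesthesia, lying flat and fasting, a subject has no current daily or social life to rate. The answer is either recall of the time before surgery or a report of acute recovery, and the article does not say which. Pain, distension, nausea and vomiting are different: they are acute postoperative symptoms, and a 6-h first value suits them.

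For the GIQLI the 6-h value is one of three levels in the repeated-measures ANOVA. The group-by-time term is built from contrasts with it. The group main effect averages over it, although no treatment effect can exist before the first session. Neither scale can show whether subjects returned to their pre-operative state. The article quotes a normal GIQLI range of 121–125, but without a pre-operative score nobody can tell whether a subject was ever in it.

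At stake are the precision and the reading of two of the eight secondary outcomes. The primary outcome is untouched.

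**Working it through.** **The plan's own figure.** n = (1.96 + 0.84)² × (2.89² + 4.31²) / 4² = 7.84 × 26.93 / 16 = 13.19, rounded up to 14. Then 14 / 0.85 = 16.5, rounded up to 17 per arm, 34 in total. This reproduces. It concerns flatus time only and does not change here.

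**Inputs from the document.** 17 per arm, 1:1 allocation, two-sided 5% level.

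**Assumptions.** The document gives no SD, correlation or effect for either scale. I assume an equal SD (set to 1) at each visit, a true effect of 0.8 SD after treatment and none at the first score, and a correlation r between the first and a later score of 0.2 to 0.6. For the three-visit main effect I also assume a correlation of 0.6 between discharge and 1 month.

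**Formulas.**
- Change from the first score: variance 2(1 − r), 32 df.
- First score as covariate: variance 1 − r², 31 df.
- Follow-up alone: variance 1, 32 df.
- Group main effect over three visits: effect (0 + 0.8 + 0.8)/3 = 0.533; variance [3 + 2(r + r + 0.6)]/9 = (4.2 + 4r)/9; 32 df.
- Power from the noncentral t, noncentrality = effect / √(2 × variance / 17). Example, change at r = 0.2: 0.8 / √(2 × 1.6 / 17) = 1.84, power 43%.

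| r | Change: variance, power | Covariate: variance, power | Main effect: variance, power |
|---|---|---|---|
| 0.2 | 1.60, 43% | 0.96, 64% | 0.556, 53% |
| 0.4 | 1.20, 54% | 0.84, 69% | 0.644, 47% |
| 0.5 | 1.00, 62% | 0.75, 74% | 0.689, 44% |
| 0.6 | 0.80, 72% | 0.64, 81% | 0.733, 42% |

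Follow-up alone: 62%.

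**Reading the table.**
1. Below r = 0.5 a change analysis does worse than having no first score at all.
2. The main effect runs the other way: it loses power as r rises. A poorly correlated first score therefore does not harm every term of the ANOVA.
3. The covariate analysis beats both terms at every r shown. Against change this is algebra: 2(1 − r) − (1 − r²) = (1 − r)², which is never negative.
4. Averaging discharge and 1 month keeps the ordering. Mean minus first score has variance 1.8 − 2r and power 48% to 83%; the adjusted mean has variance 0.8 − r² and power 74% to 93%.
5. With 14 per arm after the planned losses, one visit gives 36% to 62% on change, 55% to 72% adjusted and 53% with follow-up alone.

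**Two separate gains.** If the 6-h score had r = 0.2 and a pre-operative score r = 0.6, going from change on the 6-h score (43%) to adjustment for the same score would give 64%. Replacing it with the pre-operative score would give 81%. The second step exists only if the pre-operative score correlates better with later scores, which is plausible but not shown in the document.

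**The case against.** The strongest defence is that the trial treats dysfunction arising after surgery, so the state just before the first session is a legitimate starting point. Design and Intervention put the first evaluation immediately before the first treatment, and Randomization says allocation is revealed only once baseline evaluations are done. A pre-operative score predates the condition treated, and anxiety on the eve of surgery is not obviously a subject's usual state. This stands: the 6-h value is a valid pre-treatment value and should be kept.

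Three stronger readings are tempting but unsupported.
- **Bias.** A reader might infer that the comparison between arms is biased. It is not, for the reason just given.
- **Both scales lose power in a change analysis.** The article specifies no change analysis for HADS, so that argument applies to the GIQLI only.
- **The timing is shown to add noise, or to double the variance.** A doubling (1.6 against 0.8) needs correlations of 0.2 and 0.6. At 0.5 against 0.6 the ratio is 1.0/0.8 = 1.25. The article does not say which ANOVA term is decisive, and for the main effect a lower correlation helps.

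It can also be said that moving the questionnaires during ongoing recruitment would mix two kinds of first score in 34 subjects. That counts against moving them, not against adding a pre-operative one. Finally, the schedule figure is not shown; its legend includes the day before surgery, so what it lists there cannot be checked.

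**Conclusion.** The point holds as a cheap improvement of minor importance. The text times the first GIQLI and HADS at 6 h and gives no pre-operative score, although a contact exists the day before. For the GIQLI, whose daily-life and social items fit that moment poorly, this score enters the ANOVA as a level. Both ANOVA terms then do worse than covariate adjustment at every correlation tried. For HADS the loss is confined to interpretability and a useful covariate.

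The size cannot be derived from the document; the figures above are illustrations resting on the stated assumptions. What does not depend on the chosen correlation is that adjustment never has a larger variance than change, and that a level before treatment reduces the main effect to two thirds of its later size.

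The conflict over when the first evaluation takes place is textual, needs no assumption, and must be resolved in any case.

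**What to change.** 1. Add GIQLI and HADS at the contact the day before surgery.
2. Keep the 6-h scores as a separate early time point, and say explicitly for these two scales that they precede the first session, as is already said for the symptom scales.
3. Compare arms at discharge (both scales) and 1 month (GIQLI) with the pre-operative score as covariate, instead of entering the first score as a level of the repeated-measures ANOVA.
4. Flag subjects enrolled before the change who lack a pre-operative score, and run a sensitivity analysis with the 6-h score as covariate, which the schedule provides for everyone.
5. Reconcile the Subjects' timeline (first evaluation on day 0, the day before surgery) with Design, Intervention and Secondary outcomes (6 h after surgery). Leave the first assessment of pain, distension, nausea and vomiting at 6 h.

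Cost: a small edit to the case report form and schedule, one extra completion of two questionnaires per subject, and a few early subjects without the pre-operative value. No extra visit is needed and the sample size stays at 34.

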##### Safety indicators

An adverse event is defined as at least four subjects suffering from the same symptom—such as local skin pain, itching, ulcers, bleeding, dizziness, or hypoglycemia—during the treatment and the follow-up period. Regardless of whether the unfavorable reactions or adverse events are related to the treatment, the researchers responsible for the treatment of the subjects will keep detailed records. Based on a statistical analysis of these events, XNKQAT safety will be evaluated.

If adverse events occur, the researchers will select an appropriate treatment method until the condition is stabilized. After the subject’s condition returns to normal, the researchers will decide whether further observation is required. If serious adverse events occur, the investigators will immediately report to the IRB and manage the subject’s condition appropriately.

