### Sample size estimation and statistical analysis

#### Sample size estimation

The trial will test two groups in parallel. The following formula was used to estimate the required sample size:$$ n=\frac{{\left({Z}_{1-\alpha /2}+{Z}_{1-\beta}\right)}^2\kern0.5em \times \kern0.5em \left({\sigma}_1^2+{\sigma}_2^2\right)}{\delta^2} $$

In this formula, *n* is the number of samples in each group, σ is the standard deviation, and δ represents the difference with clinical significance between two groups. Using the parameters *α* = 0.05 and power = 80%, the corresponding Z values for a bilateral test are Z_1–α/2_ = 1.96, Z_1–β_ = 0.84. In the November 2016 pilot trial, the average times until the first postoperative flatus in the XN and SH groups were S_1_ = 2.89 h and S_2_ = 4.31 h, respectively. Based on this clinical experience, we defined 4 h as a clinically significant difference in time until first postoperative flatus between the two groups. By substituting these values into the formula above, we obtained the parameter *n* = 13.19. Rounding up to the next whole number, the number of samples in each group should be 14. Assuming a loss rate of 15%, the final number of samples in each group will be 17. Hence, the total number of subjects in the present study will be 34.

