#### Statistical analysis

##### Analysis procedures

*Sample distribution:* We will describe the size and dropout rate of each dataset. Detailed reasons for any dropouts will be provided.

*Balanced comparison:* We will compare the general subject data and then evaluate comparability between the two groups.

*Efficacy analysis:* We will use the time until the first postoperative flatus as a primary outcome to assess the efficacy of XNKQAT by intradermal needling in the treatment of gastrointestinal dysfunction after laparoscopic surgery. We will calculate the average and standard deviation to describe the outcome and use an independent-samples *t* test to compare the two groups. Eight secondary outcomes (time until first postoperative defecation; level of abdominal pain, abdominal distension, and nausea; blood ghrelin level; vomiting; psychological status; and quality of life) will be compared between the two groups to determine the efficacy of XNKQAT intradermal needling. The mean and standard deviations of these parameters will be reported. To record the subjects’ psychological status, we will record their scores and determine their classification based on the standards mentioned above. To determine the time until the first postoperative defecation, we will use the same method as the time until the first postoperative flatus. To analyze abdominal pain, abdominal distension, nausea, vomiting, ghrelin level, and quality of life, we will use repeated measures analysis of variance (RMANOVA). Before RMANOVA, we will carry out a test of sphericity to ensure that the data are suitable for this method. If the data do not meet spherical symmetry requirements, we will use the ε correction factor to correct the degrees of freedom before applying RMANOVA. The Mann–Whitney *U* test or Spearman’s Rank correlation coefficient tests will be used to analyze the categorization standards for psychological status.

*Safety analysis:* According to the definition of adverse events, specific adverse events will be listed, along with their severity level, causes, and explanations. The number of adverse events, and the adverse event rate, will be described statistically. If they need to be compared between groups, the χ^2^ test or Fisher’s exact test will be used.

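### Adverse events are defined by a four-subject threshold, so a harm seen in one to three subjects is analysed as no adverse event

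*Protocol article*

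**What the plan says.** The definition is in the protocol article under Safety indicators: "An adverse event is defined as at least four subjects suffering from the same symptom". The examples given there include skin ulcers, bleeding and hypoglycemia, and the window is treatment plus follow-up. The same paragraph asks for detailed records, "Regardless of whether the unfavorable reactions or adverse events are related to the treatment", and continues: "Based on a statistical analysis of these events, XNKQAT safety will be evaluated". The next paragraph adds: "If serious adverse events occur, the investigators will immediately report to the IRB".

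The safety analysis, under Analysis procedures, takes the definition over: "According to the definition of adverse events, specific adverse events will be listed, along with their severity level, causes, and explanations". It then says: "The number of adverse events, and the adverse event rate, will be described statistically". A chi-square or Fisher test follows if a comparison between groups is needed.

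The sample size section fixes the denominators: "the final number of samples in each group will be 17" and "the total number of subjects in the present study will be 34".

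**The concern.** An adverse event is normally an occurrence in one subject. Here it exists only once a fourth subject has the same symptom. Because the listing, count and rate all follow the definition, anything below four drops out of the reported safety result even if it was recorded.

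The definition also does not fit the text around it. Severity, cause, treatment until stable and immediate reporting of serious events all concern a single subject. Serious adverse events have no definition of their own, so it is unclear whether a serious reaction in one subject qualifies.

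The text does not say whether the four are counted within an arm or across the trial, so the numerator of the rate is undefined. Under pooled counting the rule behaves perversely. Three cases against none would be reported as no adverse event, while three against one would be reported. The sharper contrast is the one that is lost.

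The abstract names safety alongside efficacy as an aim. The rule could support a statement that no adverse events occurred when several subjects had been harmed.

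**Working it through.** **Inputs.** Threshold of four subjects (Safety indicators). SDs 2.89 h and 4.31 h, difference 4 h, Z values 1.96 and 0.84, loss 15% (Sample size estimation). The documents give no symptom risk, so p is an assumption and is shown over a range.

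**The plan's own sample size.** n = (1.96 + 0.84)² × (2.89² + 4.31²) / 4² = 7.84 × 26.9282 / 16 = 13.19, rounded up to 14. Then 14 / 0.85 = 16.5, rounded up to 17 per arm, or 34 in total. This reproduces the protocol.

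**What four subjects means.** 4/17 = 23.5% of an arm and 4/34 = 11.8% of the trial. The largest uncounted frequencies are 3/17 = 17.6% and 3/34 = 8.8%.

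**Chance of reaching the threshold.** P(X ≥ 4) = 1 − Σ C(n,k) pᵏ(1−p)ⁿ⁻ᵏ for k = 0 to 3. For n = 17 and p = 0.10 the four terms are 0.1668 + 0.3150 + 0.2800 + 0.1556 = 0.9174, so P(X ≥ 4) = 0.083. The chance of at least one case is 1 − 0.9¹⁷ = 0.833.

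| True risk | Needled arm only, n = 17: at least one case | n = 17: one to three cases (seen, not counted) | n = 17: four or more | n = 14: four or more | Both arms at equal risk, pooled n = 34: four or more |
|---|---|---|---|---|---|
| 5% | 58.2% | 57.3% | 0.9% | 0.4% | 8.8% |
| 10% | 83.3% | 75.1% | 8.3% | 4.4% | 44.6% |
| 15% | 93.7% | 69.3% | 24.4% | 14.7% | 77.1% |
| 20% | 97.8% | 52.6% | 45.1% | 30.2% | 93.0% |

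The n = 17 columns apply to a symptom that occurs only in the needled arm, whether counting is per arm or pooled, because the sham arm then adds no cases. The sham arm receives tape without needles or pressing (Control (sham) group), so this is the relevant case for needle-related skin damage and bleeding. The n = 14 column is the arm size before the allowance for loss. It matters because Statistical analysis methods assigns the safety analysis to subjects who complete the trial.

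**A single observed result.** Three affected of 17 is 17.6%, with an exact (Clopper-Pearson) 95% interval of 3.8% to 43.4%. If no sham subject has the symptom, the plan counts this as zero.

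**The case against.** The best defence is that nothing need be lost. The plan asks for detailed records of unfavorable reactions as well as adverse events. The sentence that bases the safety evaluation on these events follows directly and can be read as covering both. Serious events go to the ethics board at once, and the between-group test is only conditional. This stands as far as data collection goes: cases below the threshold can probably be recovered. It does not rescue the analysis, because the safety analysis paragraph applies the definition by name and no section analyses reactions that fall short of four. The ethics-board report is a notification rather than an analysis, and it depends on the same badly defined term.

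A second objection concerns size. Dizziness or hypoglycemia may follow surgery and fasting, and itching may follow tape, so these can occur in both arms. If they are equally likely in both and counted over 34, the threshold is reached far more often, 93.0% of the time at 20% risk. This also stands. The loss is severe for reactions specific to the needled arm at risks of about 10% or less, and much smaller for common symptoms shared by both arms.

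**Conclusion.** The concern holds. The four-subject definition is a stated rule, and following it gives a wrong safety result. For a reaction confined to the needled arm, the chance that it fails to count as an adverse event is 99.1% at a true risk of 5%, 91.7% at 10% and 54.9% at 20%. For a symptom equally likely in both arms and pooled over 34, the figures are 91.2%, 55.4% and 7.0%. These rest on assumed risks and on independence between subjects. The defect itself does not depend on them, since any symptom in one to three subjects is counted as none. The primary outcome, the sample size and the efficacy analysis are unaffected. Because safety is a stated aim, this must be corrected before the safety data are analysed.

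**What to change.** - In Safety indicators, define an adverse event as any untoward medical occurrence in an individual subject from the first session to the end of follow-up, whether or not related to treatment. Define serious adverse events at the same level.
- In the safety analysis, report by arm the number of subjects with at least one event and the number of events, overall and by symptom, with severity and cause. Give exact confidence intervals for the proportions. The intervals will say more than a test: with 17 per arm, Fisher's exact test gives p = 0.103 for four cases against none and p = 0.044 for five against none.
- Drop the four-subject threshold, or keep it as a separately named trigger for extra review and say whether it is counted per arm or overall.
- State how nausea, vomiting, abdominal pain and distension, already secondary outcomes, are handled, so that they are not counted twice.

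The cost is wording in two sections, plus a check that the case report form, which is not shown, accepts events in single subjects. Detailed records of all reactions are already required, so no new data collection should be needed. The reported event rate can only stay the same or rise.
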